### Randomisation

Quasi randomisation is conducted at the participant (workers) level at each of the three participating front offices of the Dutch SSA. Because workers with expired fixed-term contracts are registered later during the sick leave process, the Brainwork Intervention also begins later for this group. Therefore, the sick-listed workers are pre-stratified based on the type of worker (i.e., unemployed and temporary versus expired fixed-term contracts) to ensure equal distribution of the different types of workers in the control and intervention group. Because a blinded allocation is impractical and difficult to set up in the practice of the Dutch SSA, the following allocation scheme is used: the first five sick-listed unemployed and temporary agency workers with psychological problems, as identified by each participating Dutch SSA front office, and who met the inclusion criteria are allocated to the intervention group. The first five workers with expired fixed-term contracts having psychological problems are allocated to the control group. The next five sick-listed unemployed and temporary agency workers having psychological problems are allocated to the control group, while the next five workers with expired fixed-term contracts are allocated to the intervention group and so on. The person who allocated the worker to either control or experimental group is unaware of the type or severity of the psychological problem, or of any other participant characteristics.

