### Measures

#### Primary outcome

##### Duration of sick leave

The primary outcome measure in this study is duration of sick leave and operationalised as duration of the sickness benefit period (in days) from the first day of reporting sick until the end of the sickness benefit. The sickness benefit ends after a full RTW (e.g., for temporary agency workers) or if the participant is declared fit for work (e.g., for unemployed workers). Data on sickness benefit duration are continuously registered by the SSA and will be acquired from the SSA database six months after inclusion of the last participant and after a one-year follow-up period. Because the SSA registers all the data regarding sickness benefit claims, a loss of data to follow-up with regard to the primary outcome is not expected.

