##### Duration from SSA transfer to RTW

The duration from SSA transfer to RTW is operationalised as the actual duration that the sick-listed worker was under counselling by the front office of the SSA until the end of the sickness benefit. When unemployed and temporary agency workers report themselves sick, first the back office of the SSA is notified. It may take two to four weeks before the front office of the SSA receives the sick report. Only after the front office receives the report can the sickness absence counselling begin. Workers with expired fixed-term contracts (those whose contracts expired while they were sick-listed) will register at the SSA later in the sick leave process than the unemployed and temporary agency workers because the contract workers have an employer at the time of reporting sick. At this registration, the SSA receives all data from the start of the sick leave onwards, from the former employer and occupational health service related to the employer. After expiration of the fixed-term contract, the SSA becomes responsible for the sickness benefit claim, so the actual duration of SSA counselling for this sick-listed worker is shorter then the duration of sick leave. Data are continuously recorded and will be acquired from the SSA database.

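### The same opposite starting arms at every office can tilt worker type in one direction only, and the primary analysis does not reliably adjust for it

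*Protocol article*

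**What the plan says.** All references are to the protocol article.

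- **Level of allocation** (Randomisation): "Quasi randomisation is conducted at the participant (workers) level at each of the three participating front offices of the Dutch SSA".
- **Starting arm, unemployed and temporary agency workers** (same section): the first five, "as identified by each participating Dutch SSA front office, and who met the inclusion criteria are allocated to the intervention group".
- **Starting arm, fixed-term workers** (same section): "The first five workers with expired fixed-term contracts having psychological problems are allocated to the control group". The arms then swap, with the second five of the first type going to control, "while the next five workers with expired fixed-term contracts are allocated to the intervention group and so on".
- **Purpose of the stratification** (same section): "to ensure equal distribution of the different types of workers in the control and intervention group".
- **Primary outcome** (Duration of sick leave): the sickness benefit period is counted "from the first day of reporting sick until the end of the sickness benefit".
- **Late entry** (Duration from SSA transfer to RTW): "Workers with expired fixed-term contracts (those whose contracts expired while they were sick-listed) will register at the SSA later in the sick leave process". The other workers reach the front office two to four weeks after reporting sick.
- **Analysis** (Data analysis; Effect evaluation): the primary model names group as fixed factor, with the counsellor as a level above the participant. Non-returners after one year are set to 365 days. Baseline characteristics are compared, and the main analyses are adjusted for prognostic differences where this is judged needed. Worker type becomes a covariate if attrition changes the ratio of types; that rule stands in the paragraph on secondary outcomes.

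**The concern.** Alternating runs balance a list only when it stops at a multiple of ten. At any other length the arm that started is ahead. Had the starting arm varied between offices, these leads would tend to cancel. Here it is fixed by worker type and, on the natural reading, is the same at all three offices, so the leads add up. Control can only gain fixed-term workers and Brainwork can only gain unemployed and temporary agency workers. The two surpluses partly or fully offset in the arm totals, so equal group sizes would not reveal the tilt.

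Worker type is the factor on which the protocol chose to stratify, and it is plausibly related to the outcome. Fixed-term workers enter the study only if they are still sick when their contract has ended, and the time already elapsed counts towards their duration. If they do have longer recorded sick leave, a surplus of them in control lengthens the control mean for a reason unrelated to Brainwork.

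**Working it through.** **1. The plan's own figure.** The article gives 144 per group for a 40-day difference, but not the SD, alpha, sidedness or power, so the figure can be neither confirmed nor refuted. Solving n = 2·SD²·(z_α + z_β)²/δ² for the SD:
- two-sided 5%, 80% power (assumed): SD = 40·√(144/2)/(1.960 + 0.842) = 121.1 days;
- two-sided 5%, 90% power (assumed): SD = 40·√(144/2)/(1.960 + 1.282) = 104.7 days.

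With 150 per arm and independent observations, SE = SD·√(2/150), which is 14.0 or 12.1 days.

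**2. Lead of the starting arm in one list.** It depends only on list length modulo 10:

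| Length mod 10 | 0 | 1 | 2 | 3 | 4 | 5 | 6 | 7 | 8 | 9 |
|---|---|---|---|---|---|---|---|---|---|---|
| Lead | 0 | 1 | 2 | 3 | 4 | 5 | 4 | 3 | 2 | 1 |

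The lead is never negative. Its maximum is 5. Its mean is 25/10 = 2.5 if all ten remainders are equally likely (assumption).

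**3. Sum over three offices, per worker type.** Maximum 3 × 5 = 15; average 3 × 2.5 = 7.5.

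**4. Gap in fixed-term share, control minus Brainwork.** When both types have the same surplus, the arms stay at 150 each:
- maximum 15/150 = 10 points;
- typical 7.5/150 = 5 points;
- zero if every list stops at a multiple of ten.

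A simulation of 300 workers spread at random over three offices, 40,000 runs per setting, gave (fixed-term share assumed):

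| Fixed-term share | Mean gap, points | 95% range, points |
|---|---|---|
| 10% | 4.5 | 1.6 to 7.5 |
| 20% | 4.9 | 2.2 to 7.7 |
| 30% | 5.0 | 2.4 to 7.6 |
| 50% | 5.0 | 2.7 to 7.3 |

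The gap was never negative. That follows from step 2 and is not separate evidence.

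**5. Bias if unadjusted.** Bias = share gap × D, where D is the mean difference in recorded duration between worker types. The article does not give D, so the values below are assumptions. Two-sided type I error = Φ(−1.96 + bias/SE) + Φ(−1.96 − bias/SE).

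| D, days | Bias at 5 points | Bias at 10 points | Type I error at 5 points, SE 14.0 | Same, SE 12.1 |
|---|---|---|---|---|
| 0 | 0 | 0 | 5.0% | 5.0% |
| 50 | 2.5 | 5 | 5.4% | 5.5% |
| 100 | 5 | 10 | 6.5% | 7.0% |
| 150 | 7.5 | 15 | 8.3% | 9.5% |

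Against the 40-day target, the typical bias of 2.5 to 7.5 days is 6% to 19%.

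**6. What a random starting arm would do.** With one lot per office, reversing both lists together, the mean gap falls to 0. In a single trial the 95% range is still about −6 to +6 points.

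**The case against.** A reader might infer that the result will be biased towards Brainwork. The documents do not support that. The allocation arithmetic is certain, but the bias also needs D above zero. The article makes longer recorded leave in fixed-term workers plausible and gives no figure for it. The 365-day value for non-returners may also compress any difference between the types. This objection stands, so the claim is limited to what could happen.

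A reader might also infer that nothing in the plan corrects the imbalance, or that a 5-point gap would go unnoticed because it is not statistically significant. Neither holds. The Data analysis section allows adjustment of the main analyses after a descriptive comparison, with no significance threshold, and worker type is an obvious variable to look at. What remains is that the adjustment is a judgement made after the data are seen, and no criterion is given for it. The one rule that names worker type is triggered by attrition and sits with the secondary outcomes. An imbalance that comes from allocation is not clearly covered by it, and no loss of primary outcome data is expected.

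It can further be said that a journal article may leave the full covariate list to an analysis plan. That is fair, and the absence of a list is not the point here. The point is an allocation rule that works against its own stated aim, together with adjustment rules that, as written, are conditional.

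Finally, the effect is small: on the figures above, the typical bias is about 0.2 to 0.5 of a standard error with SE 14.0. This stands too.

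**Conclusion.** The concern holds in a limited form. The scheme creates a bounded worker-type imbalance that can run in one direction only: 0 to 5 workers per list and at most 15 per type. The fixed-term share in control is therefore higher by at most 10 points, and by about 5 points if stopping points are arbitrary. This works against the equal distribution that the stratification is meant to secure.

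Left unadjusted, the imbalance could favour Brainwork by about 2.5 to 7.5 days at the typical gap. Two-sided type I error would then be about 5.4% to 8.3% with an SE of 14 days. These sizes rest on an assumed D of 50 to 150 days, an SD back-solved under assumed error rates, and independent observations. They shrink if the 365-day value compresses D and vanish if D is zero. Confidence is high for the direction and bounds of the imbalance, and only moderate for any effect on the result. The point does not invalidate the trial, but it is easily closed.

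**What to change.** - **Effect evaluation.** Include worker type as a fixed covariate in the primary model whatever the observed balance, and preferably office as well. Worker type is already the stratification factor. As a covariate it removes the additive shift whichever arm each list started in, and also for workers already allocated.
- **Reporting.** Show the number of workers of each type by arm and office, so that the remaining imbalance is visible.
- **Randomisation.** For any list not yet started, draw the starting arm by lot. This removes the systematic direction but not the imbalance in a single trial, so it supplements the covariate and does not replace it. If the two lists at an office are drawn independently, the offset in arm totals is no longer guaranteed.

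The cost is one or two model terms, one table, and at most six lots. No extra participants or data are needed.

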### Blinding

Participants, OH professionals and intervention partners such as vocational rehabilitation agencies and mental health institutions/professionals are not blinded to the intervention. Blinding was deemed unnecessary because the Brainwork Intervention contains several new elements compared to usual care including, category classification, a protocol-based approach and contracting of vocational rehabilitation agencies. Because the SSA registers sickness benefits, these measurements are derived from the computerised SSA database. Therefore, any bias due to lack of blinding is prevented for the primary outcome. Furthermore, most secondary outcome measures are self-reported, and thus, blinding to the participant groups is not possible. After inclusion in the study, all participants receive a research code. All data will be entered in the computer by a research assistant, using this research code, in order to guarantee that analyses of the data by the researcher will be anonymous.

### Measures

#### Primary outcome

##### Duration of sick leave

The primary outcome measure in this study is duration of sick leave and operationalised as duration of the sickness benefit period (in days) from the first day of reporting sick until the end of the sickness benefit. The sickness benefit ends after a full RTW (e.g., for temporary agency workers) or if the participant is declared fit for work (e.g., for unemployed workers). Data on sickness benefit duration are continuously registered by the SSA and will be acquired from the SSA database six months after inclusion of the last participant and after a one-year follow-up period. Because the SSA registers all the data regarding sickness benefit claims, a loss of data to follow-up with regard to the primary outcome is not expected.

#### Secondary outcomes

##### Proportion of subjects returned to work

The proportion of the subjects who returned to work is operationalised as the proportion who ended sickness benefit claims and will be measured at 8 and 12 months after the date that the SSA received the sick report. Data are acquired from the SSA database.

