### The Dutch social security system

In the Netherlands, the Sickness Benefits Act provides assistance for sick-listed workers without an employment contract. The Social Security Agency (SSA) provides a sickness benefit during the first two years of sickness absence. There are no legislative mandates for these workers to be returned to their previous/last job. Therefore, the SSA is also responsible for sickness absence counselling, which is usually conducted by an insurance physician (IP).

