#### Rationale of the Brainwork Intervention

Hereafter, the intended mechanisms of the Brainwork Intervention components are described. (1) Face to face contact: by having a personal conversation at an early stage, the worker will feel as if his problems are taken seriously. This contact encourages the worker to make the required commitment to the intervention, which is required for achieving a positive outcome. (2) Category classification: shortly after inclusion of the worker in the program, the IP classifies the worker into a category based on the IP’s assessment of the worker’s functional impairments and estimated recovery time. A stepped care approach is used, which allows a worker with an estimated favourable recovery (estimated recovery within 3 months) to receive less intense and shorter sickness absence counselling. The classification delineates other elements of the Brainwork Intervention, namely goal-setting, increasing the efficiency of SSA work processes and worker referrals to specific interventions. The IP is asked to provide a recovery estimation of the worker based on the severity of his psychological problems and functional impairments, as well as RTW prognostic factors such as health expectations, RTW expectations and the perceived health of the worker, age, and personal factors such as education level [3,20,23]. (3) Motivate to activate: this element is designed to provide active day care for the worker. In groups with varying psychological disorders, it has been demonstrated that activation promotes recovery from mental complaints and increased functioning [24,25]. (4) Goal-setting: setting explicit goals regarding activity level of the worker and the final RTW date (or maximum duration of the sickness benefit period) is part of the Brainwork Intervention. Defining the expected recovery period will give the Brainwork participant a better perspective on his recovery, increase his sense of control, encourage a faster recovery and reduce the number of psychological complaints [26-28]. (5) Providing advice for daily structure: Brainwork participants are advised to maintain a good day structure by getting up at a specific predetermined time and planning an activity for the morning. The activity can be, for example, a visit to the gym but is not limited to exercise. This advice creates a better day-structure for the worker and may promote the recovery from mental complaints and increased functioning [24,25]. (6) Guidance to work: because work is a structuring activity, it is considered to have a positive impact on the recovery from mental complaints and increased functioning because it leads to a clear day-structure and more active day care. In addition, having a work perspective focuses the worker on improving, which has a positive effect on recovery from complaints and improved functioning. Furthermore, because there is a fast start of activities aimed at RTW and paid labour, a shorter duration of sick leave is anticipated. (7) Increased efficiency of the internal SSA work process: by optimizing the collaboration between multiple OH professionals, the prompt handling of requests regarding sickness benefit claims and quick referral to external intervention partners reduces the turnaround time and facilitates early RTW. (8) Timely referral for interventions: depending on the initial category classification of the worker, a protocol-based quick referral to external intervention partners may follow for those workers for whom a quick recovery is not expected. This method promotes a quick start of the Brainwork Intervention and is considered to have a positive effect on the mental complaints and functional recovery of the worker.

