### Study population

The population in this study consists of unemployed and temporary agency workers and workers with expired fixed-term contracts, who live in the eastern, south-western or southern part of the Netherlands and when sick-listed are the responsibility of the three participating front offices of the Dutch SSA. The inclusion criteria are: (1) being an unemployed or temporary agency worker or worker with an expired fixed-term contract; (2) between 18 and 64 years of age; (3) sick-listed and not expected to RTW within two weeks after reporting sick or contact with the vocational rehabilitation counsellor of the SSA; (4) having psychological problems/complaints as the main reason for a sickness benefit claim; and (5) adequate command of the Dutch language. The exclusion criteria are: (1) recent pregnancy or up to three months after delivery; (2) substance addiction (alcohol, drugs and medicines) as the main reason for a sickness benefit claim; (3) having a severe psychiatric disorder with an expected recovery of more than one year (e.g., hospitalization or day treatment).

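### The return-to-work proportion counts every ended benefit claim as a return, so a late-transferred worker still unfit at the two-year benefit limit would be scored as returned to work

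*Protocol article*

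**What the plan says.** Four statements in the protocol article bear on this point.

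- **Outcome definition** (Proportion of subjects returned to work): the outcome has this definition: "operationalised as the proportion who ended sickness benefit claims and will be measured at 8 and 12 months after the date that the SSA received" (their sick report). The reason for ending plays no part.
- **Benefit limit** (The Dutch social security system): "The Social Security Agency (SSA) provides a sickness benefit during the first two years of sickness absence". The limit runs on absence, not on time since the SSA took over. The Rationale of the Brainwork Intervention also mentions a maximum: "the final RTW date (or maximum duration of the sickness benefit period".
- **Late entry** (Duration from SSA transfer to RTW): workers with expired fixed-term contracts "will register at the SSA later in the sick leave process than the unemployed and temporary agency workers". At that registration "the SSA receives all data from the start of the sick leave onwards", so part of the two years has already been used.
- **Ways the benefit ends** (Duration of sick leave): "The sickness benefit ends after a full RTW (e.g., for temporary agency workers) or if the participant is declared fit for work". Reaching the two-year limit is not on this list.

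**The concern.** The outcome is read on a clock that starts at SSA receipt, while the benefit runs out on a clock that starts on the first sick day. For a worker who enters late enough, the second clock runs out before the first reaches its reading. The claim has then ended although the worker neither resumed work nor was declared fit. Taken as written, the definition scores this as a success, when exhausting the benefit while still unfit is among the poorest outcomes a participant can have.

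Among workers received 12 or more months into absence, every claim has ended by the 12-month reading, whatever the intervention did. That subgroup would show 100% return to work in both arms and add nothing to the comparison.

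**Working it through.** The plan gives no figure of its own for this point. The planned sample of 300 serves only as a denominator.

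**Inputs from the article:** benefit limit of 2 years from the start of absence (24 months, 730 days); readings at 8 and 12 months after SSA receipt. For fixed-term workers, receipt is taken to be the registration at the SSA when the contract expires.

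**Threshold.** The limit falls on or before a reading when absence before receipt is at least 24 months minus the reading time.

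- 12-month reading: 24 − 12 = 12 months (730 − 365 = day 365).
- 8-month reading: 24 − 8 = 16 months (730 − 243 = day 487).
- Workers received at month 3, 6 or 9 have 21, 18 or 15 months of possible benefit left and are not affected.

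**Example.** First sick day is day 0, SSA receipt is day 450, and the worker never recovers.

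- The limit is reached on day 730, which is 730 − 450 = 280 days after receipt.
- 8-month reading: 450 + 243 = day 693. The claim is open, so the worker is scored not returned.
- 12-month reading: 450 + 365 = day 815. The claim has ended, so the worker is scored returned to work.

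**Eligibility.** The Study population section sets no upper limit on absence before inclusion. It excludes "having a severe psychiatric disorder with an expected recovery of more than one year", which concerns one diagnostic group and an expected rather than an actual course.

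**Size.** The article gives none of the shares needed, so all three are assumptions: fixed-term workers 10–50% of the sample; 0–25% of these received at 12 months or later; 30–100% of those still unfit at the limit. The overstatement of the 12-month proportion is the product of the three.

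| Fixed-term | Received at ≥12 months | Still unfit at limit | Overstatement | Workers of 300 |
|---|---|---|---|---|
| any | 0% | any | 0 points | 0 |
| 20% | 10% | 30% | 0.6 points | 1.8 |
| 33% | 10% | 60% | 2.0 points | 5.9 |
| 50% | 10% | 60% | 3.0 points | 9.0 |
| 50% | 25% | 100% | 12.5 points | 37.5 |

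The last row puts every share at its maximum and is an outer bound.

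**Dilution.** If late entrants make up a share s of each arm and the true effect is the same in them as in others, the observed difference is (1 − s) times the true one. With 33% × 10%, s = 3.3% and the contrast shrinks by 3.3% of its size.

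**The case against.** The strongest reply is that the decisive premise is missing. The article says only that fixed-term workers register later than the others, whose reports reach the front office in two to four weeks. Month 4 or month 9 is also later, and neither is affected. The intervention is described as acting early in sick leave, and it applies only to categories with an estimated recovery of up to 12 months. This stands as a limit on size: the number affected may be zero. It does not repair the definition, because late entry is not ruled out and the prognostic criteria rest on expected recovery.

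A second reply is that ended claims may be meant in the sense of the two endings listed for the primary outcome. That list describes how benefits end. It does not restrict the return-to-work definition, and it does not fit the two-year limit stated in the Background. The scoring of an exhausted benefit therefore follows from reading the sections together; no sentence says it outright.

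A third reply is that such detail belongs in an analysis plan. The article, however, does not leave the definition open. It fixes one, and that one gives the wrong score in this case.

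Two stronger readings are tempting but not supported:

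- **Primary outcome.** A reader might infer that these workers enter the primary analysis as completed spells of 730 days. The Effect evaluation section imputes 365 days for all participants not returned to work after one year of follow-up. On its wording, a worker who never recovered falls under that rule. The article does not say that the rule borrows the ended-claim definition.
- **Bias towards one arm.** Allocation is pre-stratified by worker type at each office, and both types alternate between arms. This does not balance transfer time itself, but nothing in the article suggests that it differs by arm.

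**Conclusion.** The point holds as a defect in one secondary outcome definition. As written, it would score an unrecovered worker as returned to work if the SSA received that worker 12 or more months into absence (12-month reading) or 16 or more months (8-month reading). These thresholds follow from the article's own figures.

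How often this happens cannot be known from the article. Under the assumed shares it runs from none to a few percent of the 300 in moderate cases, with 12.5% as an outer bound. The expected consequence is a return-to-work proportion that is somewhat too high in both arms and a slightly diluted contrast. No distortion of the primary outcome is established.

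**What to change.** - In the return-to-work definition, score a claim that ended because the two-year limit was reached (730 days from the first sick day) as not returned to work at both 8 and 12 months.
- Reconcile the list of benefit endings under Duration of sick leave with the two-year limit in the Background.
- In Effect evaluation, state that exhausting the benefit does not count as having returned to work. The imputed value itself need not change for this purpose.
- Report the distribution of time from first sick day to SSA receipt, so that readers can see whether any worker was affected.

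The cost is one derivation rule and a few words. The first sick day and the claim end date are already in the SSA database. Trial conduct does not change, and if no worker reaches the limit the results are identical. If some do, the return-to-work proportions become slightly less favourable.
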